### Secondary outcome measures

Secondary outcomes and the instruments that will be used for their assessments are described in tables 1 and 2. Briefly, secondary endpoints related with the study’s feasibility will be measured, namely time of follow-up, implemented sessions and complete assessment of participants (table 1). Additionally, cognitive function, quality of life, symptoms of anxiety and depression, as well as functional capacity to perform basic ADLs will be evaluated through questionnaires validated for the Portuguese population (table 2). Physical condition, blood pressure and anthropometrics will be ascertained by trained interviewers. Levels of glycated haemoglobin, and 24-hour urinary excretion of sodium and potassium will be also measured. The secondary outcomes described on the table 2 will be also measured at baseline and follow-up at 3 months.

**Table 1 T1:** Description of the secondary feasibility outcomes

Outcome	Description
Time of follow-up	Calculated by the number of days between the participant’s first and last session attended.
Implemented sessions	Proportion of sessions implemented, calculated as the number of sessions that the research team was able to implement divided by the total number of sessions planned.
Complete assessment of participants	Proportion of participants with full information at baseline and follow-up points, calculated by dividing the number of participants with complete information by the number of participants evaluated.

**Table 2 T2:** Description of the instruments used for the evaluation of secondary outcomes

Outcome	Instrument	Description
Cognitive performance	MoCA^29–31^	Brief screening tool to detect mild cognitive impairment. It assesses eight cognitive domains: visuospatial ability, executive function, attention, concentration, working memory, language, verbal memory and orientation, with scores from 0 to 30. Higher scores represent better cognitive performance, and one point is added for participants with less than 12 years of education.
	Brain on Track^21 32^	Self-administered computerised cognitive test for remote longitudinal assessment. It evaluates different cognitive domains through exercises, such as attention, memory, executive functions, language, calculation, constructive capacity and visuospatial processing. The score range is the maximum number of correct answers within a limit of time. Higher scores are representative of better cognitive performance.
Memory issues	Subjective Memory Complaints Scale^19 33^	This scale comprises 10 questions regarding subjective issues of memory. This scale varies from 0 (best score) to 21 points (worst score).
Adherence to the Mediterranean diet	MEDAS questionnaire^17^	The MEDAS questionnaire is composed by 14 questions associated with eating habits and frequency of food consumption. The score ranges between 0 (lowest adherence to the Mediterranean diet) and 14 points (highest adherence to the Mediterranean diet). A score greater than nine points demonstrates a good adherence to the Mediterranean diet.
Anxiety and depression	HADS^18^	Scale with 14 questions, subdivided in two subscales: anxiety (HADS-A) and depression (HADS-D). This scale varies from 0 (best score) to 21 (worst score) for each subscale. The optimal cut-off points differ significantly in the literature. For this study, a score higher than or equal to 11 represents a case of anxiety or depression, as applicable.
Reported quality of life	EQ-5D-5L^20 34^	This scale is subdivided into two subscales: (a) five multiple-choice questions, with five response options, which results in a score that fluctuates from 5 (best score) to 25 points (worst score). One digit is provided for each dimension, combining in a 5-digit code. A total of 3125 possible health states are delineated to describe the patient’s state of health. (b) Vertical Visual Analogue Scale, which varies from 0 (worst score) to 100 (best score).
Disability	Modified Rankin Scale^35 36^	Simple scale that assesses functional capacity, referring to limitations in ‘activity and changes in lifestyle’. The scores run from 0 (perfect health) to 6 (dead). It will be considered disability as an mRS of >1 and a one-point change on the scale will be clinically significant.
Handgrip strength	Dynamometer^37–39^	Force applied in each hand in kilograms using the JAMAR dynamometer. The handgrip can be a relevant predictor of the physical function of the upper body and influences the capacity to perform ADLs. Participant will be in a seated position with the elbow flexed at 90°. Three alternating hand sequential measurements will be performed and registered. It is relevant to document the dominant hand and the affected and non-affected hands if the case.
Agility	TUG^40^	It consists of counting the participant’s time to complete the following routine: standing up from a chair, walking for 3 metres (following the marks on the floor), returning to the chair and sitting down as fast as possible. It provides important information about functional capacity, gait, dynamic balance and speed. The time will be counted from when the participant’s back leaves the chair until sitting again with their back supported. It will be considered a cut-off level of ≤10 s to identify normal mobility.
	Unipedal stance test^41^	This test is performed in time units (seconds) and the score varies from 0 (worse score) to 45 s (best score). The researcher will use a stopwatch and count the amount of time the participant can stand on one leg, of their choice, with their eyes open.
	Senior Fitness Test^42 43^	Variation of participant’s agility and dynamic balance assessed using the 8-foot distance test (2, 44 metres) from the Senior Fitness Test.
Lower limb function	Short Physical Performance Battery^44^	This battery assesses the lower limbs’ balance, gait, speed, endurance and strength. The SPPB measures three timed tests: balance in the standing position, walking speed and chair stands. Each test is scored between 0 and 4, total score ranges from 0 (poor performance) to 12 (best performance).
Functional fitness	Senior Fitness Test^42 43^	Variation of participant’s upper/lower body strength, flexibility and aerobic endurance assessed through the different tests from the Senior Fitness Test.
Functional capacity to perform basic ADLs	Barthel Index^45^	Measures functional independence on the basic ADLs. The scores vary from 0 to 20; higher scores represent increased functionality and independence.

ADLs, activities of daily living; EQ-5D-5L, Measure of health-related quality of life of the EuroQol Group; HADS, Hospital Anxiety and Depression Scale; MEDAS, Mediterranean Diet Adherence Screener Questionnaire; MoCA, Montreal Cognitive Assessment; mRS, modified Rankin Scale; SPPB, Short Physical Performance Battery; TUG, Timed Up and Go test.

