Taken together, these findings highlight the importance of multidomain interventions aiming to promote functioning levels among patients with TIA or minor stroke, and to develop preventive actions and health promotion plans specifically designed for this group. As such, this pilot study primarily aims to explore the feasibility and the effectiveness of an innovative multidomain intervention programme, composed of five strategies: cognitive training, physical exercise, nutrition education, psychoeducation and assessment/correction of hearing problems. These are aimed at accelerating the return to pre-event functionality in patients with a TIA or a minor stroke diagnosis. The primary objectives are as follows:

To assess the feasibility of methodology for early recruitment, collecting information and delivering the interventions.To estimate the effectiveness of this programme on the time to recovery in each instrumental ADLs.

As secondary objectives, the effect of this intervention on cognitive function, adherence to the Mediterranean diet, physical function, basic ADLs, symptoms of anxiety and depression, quality of life, anthropometric measures and blood pressure, will be also assessed.

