### Intervention

The intervention will be implemented over 3 months and will comprise five different components, including cognitive training, physical exercise, nutritional education, psychoeducation and assessment and correction of hearing problems. Only the intervention group will be exposed to all or any of the components of this comprehensive intervention programme. Both groups will continue to receive the usual standard of care provided to this type of clinical disease in the hospital setting. The usual standard of care consists of the initiation of the appropriate secondary prevention and referral to the outpatient cerebrovascular diseases clinic (telephone call at 1-month post-event and in-person appointment at 3 months post-event). Depending on the clinical presentation and neurological deficits, patients can also be referred to an outpatient physical medicine and rehabilitation appointment.

Since early intervention post-vascular event is decisive, given the time interval between neurological injury and the onset of nervous function recovery activities, intervention sessions are aimed to begin within no later than 15 days after the cerebrovascular event. Considering this timeline, once the participants are recruited and randomised, the intervention will start immediately, especially cognitive training.

To minimise refusals and losses to follow-up, all evaluations and sessions will be scheduled by the participant’s preference. A written plan with the intervention schedules will be given and sessions reminded through email or phone messages in the day before (day, time and location). If one intervention session is missed, efforts will be placed to arrange another suitable time in another group and individualised meetings will be rescheduled. If not possible, the missed appointment will be documented, and the dropout or non-compliance reasons will be registered for further analysis.

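### The 5–25 EQ-5D-5L score in Table 2 is an unweighted sum of level labels: it merges 3125 profiles into 21 values and gives no basis for equal weights.

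*Protocol article*

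**What the plan says.** Quality of life is among the secondary objectives at the end of the Introduction: "physical function, basic ADLs, symptoms of anxiety and depression, quality of life, anthropometric measures and blood pressure, will be also assessed". The instrument is the EQ-5D-5L, described in Table 2 under Secondary outcome measures. That cell gives three outputs:

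- **A numeric score** for the descriptive part: "five multiple-choice questions, with five response options, which results in a score that fluctuates from 5 (best score) to 25 points (worst score".
- **A profile**: "One digit is provided for each dimension, combining in a 5-digit code", followed by "A total of 3125 possible health states are delineated to describe the patient’s state of health".
- **A separate overall rating**: "Vertical Visual Analogue Scale, which varies from 0 (worst score) to 100 (best score".

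On timing, the section states: "The secondary outcomes described on the table 2 will be also measured at baseline and follow-up at 3 months".

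The cell does not use the word sum, and it names no value set, no index and no rule for analysing the profile. The section Data analysis and sample size does not mention the EQ-5D-5L.

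**The concern.** The 5–25 figure is the only single number the article defines for the descriptive part. It treats the digits as quantities. In the same cell they are labels, one per dimension, that together name a health state. The response options are ordered, so a higher digit is worse. Order alone does not show that the step from 1 to 2 is worth the same as the step from 4 to 5, or that a step in one dimension is worth the same as a step in another. A plain sum assumes both.

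If the sum became the quality-of-life outcome, patients with very different profiles would count as equally well, and the result would rest on weights that nobody chose or defended. The intervention acts through several routes ("cognitive training, physical exercise, nutritional education, psychoeducation and assessment and correction of hearing problems"), so effects confined to particular dimensions are plausible, and a total does not show where they lie. The study is also meant to inform a full-scale trial, so a weak scoring rule could be carried forward.

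**Working it through.** **Inputs.** All come from the EQ-5D-5L cell of Table 2: five questions, five response options each, score range 5 to 25, one digit per dimension, 3125 states.

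**1. Reproduce the stated figures.**
- Number of profiles: 5^5 = 3125, as stated.
- Smallest sum of five digits coded 1–5: 5 × 1 = 5. Largest: 5 × 5 = 25. Both ends agree with the stated range.
- The 5-digit code runs from 11111 to 55555, so the 5–25 score cannot be the code. Addition is an inference, but a firm one.

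**2. Count how many profiles share a score.** There are 25 − 5 + 1 = 21 possible sums. The number of profiles with sum *s* is the coefficient of x^(s−5) in (1 + x + x² + x³ + x⁴)^5.
- *s* = 9: C(8,4) = 70.
- *s* = 10: C(9,4) − 5·C(4,4) = 126 − 5 = 121.
- *s* = 15: C(14,4) − 5·C(9,4) + 10·C(4,4) = 1001 − 630 + 10 = 381, the maximum.

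Enumerating all 3125 profiles gives the same counts:

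| Score | 5 | 6 | 7 | 8 | 9 | 10 | 15 |
|---|---|---|---|---|---|---|---|
| Profiles | 1 | 5 | 15 | 35 | 70 | 121 | 381 |

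Only 11111 and 55555 have a score to themselves. The other 3123 profiles share theirs.

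**3. Look inside one score.** Ignoring which dimension is affected, the 70 profiles at score 9 have five severity patterns:
- 11115: one dimension at the worst level, the rest at the best
- 11124
- 11133
- 11223
- 22221: four dimensions one level below the best

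Check: 1 + 1 + 1 + 1 + 5 = 9 and 2 + 2 + 2 + 2 + 1 = 9.

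**4. What the tie assumes.** Let v_d(k) be the loss from being at level k rather than level 1 in dimension d. Then 11115 and 22221 are equally bad only if v_5(5) = v_1(2) + v_2(2) + v_3(2) + v_4(2). The sum sets v_d(k) = k − 1 for every d, which gives 4 = 1 + 1 + 1 + 1. The article offers no support for that choice.

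**5. Compare with the protocol's own practice.** Under Primary outcome measures, the article sets aside the total of the Frenchay Activities Index (FAI) and analyses each activity separately, because the effect on each activity is of interest. The same reasoning applies to the five EQ-5D-5L dimensions.

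No replacement score can be calculated here, because a weighted index needs a value set and the article names none.

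**The case against.** The strongest reply is that Table 2 describes instruments, not analyses. A reader might infer that the arms will be compared on the 5–25 sum, so that the trial could not say whether quality of life improved. The document does not support that reading: no comparison on this score is stated anywhere, and the choice among sum, profile, index and VAS may be made in a fuller document that is not shown. This objection stands. What remains is that the article does define a numeric score and defines it poorly; that is a stated rule, not an omitted detail.

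A second reply is that the profile and the VAS appear in the same cell, and nothing says the sum replaces them. This also stands, and it means the information can be recovered from data already planned.

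A third reply concerns cancellation. A reader might infer that the sum has the particular fault of letting a gain in one domain hide a loss in another. That is true of any single summary, including a weighted index and the VAS. Mood, mobility, lower-limb function and basic activities of daily living also have their own instruments in Table 2, so opposite movements in those areas need not go unseen. Cancellation is therefore not the ground for this point; unjustified equal weighting is.

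Finally, the counts in the working treat all 3125 profiles alike. Entry is limited to NIHSS ≤3, mRS 0–2 and discharge home, so scores may cluster near 5 (an assumption). Scores 5 to 8 cover 1 + 5 + 15 + 35 = 56 profiles, and scores 5 to 10 cover 56 + 70 + 121 = 247. The merging is smaller there but still present.

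**Conclusion.** The point holds as a weakness of scoring. The 5–25 figure is an unweighted sum of ordered labels. It weights every step and every dimension equally without a stated reason, and it reduces 3125 profiles to 21 values. It is a minor-to-moderate matter: one secondary outcome in a pilot of 70, with no sample-size figure or primary endpoint depending on it. An unweighted level sum can still serve as a rough descriptive summary of severity if it is labelled as one.

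The conclusion rests on one inference, that the score is formed by addition, which the range and the code format make firm. It does not require that the true step sizes are known to differ, only that the article gives no ground for taking them as equal. No effect on a trial result has been shown.

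**What to change.** In the EQ-5D-5L row of Table 2, and in the analysis text that follows from it:

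1. Do not use the 5–25 sum as the quality-of-life outcome. If it is kept, call it an unweighted, descriptive level sum.
2. Report the descriptive system by dimension and arm at baseline and 3 months, in line with the item-by-item analysis of the FAI.
3. Report the 0–100 VAS separately, as the patient's overall rating.
4. If a single score for the descriptive part is wanted, use an index from a named value set applicable to the population.
5. State before the arms are compared which of these outputs will be compared.

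The cost is wording and a few more lines of reporting; no new data or visits are needed. The drawback is several dimension-level comparisons in a small sample, which should be read as exploratory.

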### Blinding

Due to the nature of the present intervention, it will not be possible to guarantee a proper blinding to the intervention arm among participants; nevertheless, allocation group will not be actively reported. Regarding the outcomes assessment, interviewers will be independent and blinded to each participants’ allocation group.

### Data analysis and sample size

The associations between the social and clinical characteristics and feasibility (eg, recruitment time frame, adherence, dropouts) and lifestyle outcomes will be quantified through linear or logistic regression models, as applicable. Time in days from the onset of symptoms to complete or partial recovery in each instrumental ADLs will be estimated and illustrated by Kaplan-Meier survival curves. The time comparison between intervention and control groups will be made through the log-rank test. To estimate the association between the intervention and the recovery time, HRs will be estimated, through the computation of univariate and multivariate Cox regression models.

Training of the interviewers and use of standardised procedures for data collection is expected to contribute to a low proportion of missing data, and no imputation is being planned.

To the best of our knowledge, there is no previous information regarding effect sizes and SDs regarding the primary outcome related with the recovery of functionality after a TIA or a minor stroke. Nevertheless, a sample size of at least 70 participants (35 per arm) is commonly recommended for a pilot study when estimating the pooled SD.^25^ Nevertheless, taking into account the results of a previous RCT evaluating a cardiac model of rehabilitation for reducing risk factors post-TIA and stroke,^26^ this sample size will allow to detect mean differences of 5.5 and 6.0 in the changes observed in the Hospital Anxiety and Depression Scale—anxiety and depression scores, respectively, between intervention and control groups (assuming a statistical power of 80% and a level of significance of 5%).

To achieve the sample size needed to accomplish the proposed objectives, we expect to invite approximately 100 individuals, since a participation of 70% was previously observed in the EPIPorto cohort.^27^ We also expect a dropout of 10% from baseline to the first follow-up; nevertheless, and in order to minimise refusals and losses to follow-up, all activities will take place near participants’ residence and be scheduled for their convenience.

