### Randomisation

The participants will be randomly assigned (1:1) to the intervention or control group after the baseline assessment. Randomisation will be done using a computer-generated programme, using random blocks of four sizes. A researcher who is not immediately engaged in the project will implement the randomisation process.

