### Primary outcome measures

The primary outcomes for the study are related with its feasibility and time to partial or complete recovery of each instrumental ADLs.

To evaluate the feasibility of this study, the following primary outcomes will be assessed:

Recruitment time frame: proportion of participants recruited within 7 days after onset of symptoms. It will be assessed by dividing the number of participants recruited within the time frame divided by the total number of participants.Beginning of the intervention: proportion of participants that started any of the interventions no later than 15 days after onset of symptoms.Adherence to each component of the intervention: proportion of adherence to each component of the intervention and different intervention modalities (remote/in person), calculated as the number of sessions attended divided by the total number of sessions provided. For the COGWEB training, the outcome will be the absolute number of sessions.Dropout: proportion of participants who dropped out of the study, calculated as the number of participants who dropped out after attending at least one session divided by the total number of participants who attended at least one session.

Time to recovery in each instrumental activity of daily living will be measured by an adapted version of the Frenchay Activities Index (FAI). The translated and validated version of the FAI—adapted version for the Portuguese population^23^ will be used to assess the instrumental ADLs functional performance at baseline and follow-up at 3 months. The version used in this study is based on the perception of the patient’s capacity to perform a specific instrumental ADLs instead of its frequency, as stated in the original scale developed by Holbrook and Skilbeck.^24^ The scale consists of 15 activities, scored from 1 to 4 (1-could not do at all; 2-very difficult; 3-a little difficult; 4-not difficult at all).^23^ Although the original index suggests that total scores for men and women should be considered separately,^24^ in the present study the score of each activity will be analysed independently, as the interest in exploring the impact of the programme in each activity.

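### Logistic regression of dropout on patient characteristics would rest on about 3 to 4 events among session attenders, too few for usable odds ratios (minor; the dropout proportion itself is unaffected)

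*Protocol article*

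**What the plan says.** The Data analysis and sample size section opens with a regression plan: "The associations between the social and clinical characteristics and feasibility (eg, recruitment time frame, adherence, dropouts"), together with lifestyle outcomes, are to be quantified through linear or logistic models, whichever applies. It sets no limit on the number of characteristics and names no alternative for outcomes with few events.

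The Primary outcome measures section introduces its feasibility list with "To evaluate the feasibility of this study, the following primary outcomes will be assessed". Dropout is on that list: the count of people who leave once they have been to a session is "divided by the total number of participants who attended at least one session". The Intervention section says that only the intervention group is exposed to any component of the programme.

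On numbers, the Data analysis and sample size section states that "a sample size of at least 70 participants (35 per arm) is commonly recommended for a pilot study", that "we expect to invite approximately 100 individuals, since a participation of 70% was previously observed in the EPIPorto cohort", and "We also expect a dropout of 10% from baseline to the first follow-up". The Randomisation section says: "The participants will be randomly assigned (1:1) to the intervention or control group after the baseline assessment".

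**The concern.** Dropout is binary for each participant, so of the two models offered the logistic one applies. What a logistic model can estimate depends on the size of the rarer category, not on the number enrolled. Here the rarer category is the dropouts, and the protocol's own figures make it a handful of people. The better retention goes, the less the model can estimate.

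At stake is what the pilot reports about who leaves the programme. With 3 or 4 dropouts, a characteristic that happens to be shared by all or none of them gives an infinite or zero odds ratio. A 3-to-1 split gives an odds ratio that looks large but is compatible with almost anything. Such figures could be carried into planning of the full-scale trial as if they were informative.

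**Working it through.** **Inputs from the protocol article**
- About 100 invited, 70% participation, 1:1 allocation, 35 per arm.
- 10% dropout from baseline to first follow-up.
- Dropout denominator: participants with at least one session, so the intervention arm only.

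**Inputs assumed**
- The 10% applies to session attenders.
- Characteristics are not listed, so binary ones are given prevalences of 50%, 30% and 20%.
- No true association, unless stated.

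**1. The plan's sample size.** 100 × 0.70 = 70, and 70 / 2 = 35 per arm. This reproduces. The plan states no event count for dropout.

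**2. Expected dropouts.** 35 × 0.10 = 3.5. The binomial 95% range is 0 to 7. P(none) = 0.9^35 = 2.5%, P(4 or fewer) = 73% and P(10 or more) = 0.2%. Over all 70, which is not the outcome's definition, 70 × 0.10 = 7 (range 3 to 12).

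**3. Chance of no finite odds ratio for one binary characteristic.** With groups of size a and b and dropout probability 0.10 in each, one group or both has no dropouts with probability 0.9^a + 0.9^b − 0.9^(a+b).

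| Total | Groups | Sum | Result |
|---|---|---|---|
| 35 | 18 / 17 | 0.150 + 0.167 − 0.025 | 29% |
| 35 | 10 / 25 | 0.349 + 0.072 − 0.025 | 40% |
| 35 | 7 / 28 | 0.478 + 0.052 − 0.025 | 51% |
| 70 | 35 / 35 | 0.025 + 0.025 − 0.001 | 5% |
| 70 | 21 / 49 | 0.109 + 0.006 − 0.001 | 11% |
| 70 | 14 / 56 | 0.229 + 0.003 − 0.001 | 23% |

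Simulation agrees to within about one percentage point. With a true odds ratio of 3 and 35 attenders, the simulated chance is 42%, 30% and 30% at the three prevalences.

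**4. Precision when an estimate exists.** SE(log OR) = √(1/a₁ + 1/a₀ + 1/b₁ + 1/b₀), summed over the four cells.
- Four dropouts split 2/2 over groups of 18 and 17: SE = √(1/2 + 1/16 + 1/2 + 1/15) = 1.06; OR 0.94, 95% CI 0.12 to 7.5.
- Split 3/1: SE = √(1/3 + 1/15 + 1/1 + 1/16) = 1.21; OR 3.2, 95% CI 0.30 to 34.
- In simulation with 35 attenders the median SE is 1.21 to 1.24. exp(1.96 × 1.21) = 10.7, so about 11-fold either side. With 70, the intervals run about 5- to 7-fold either side.

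**5. One continuous characteristic.** Separation occurs in only about 3% of simulated trials with 35 attenders. SE per standard deviation ≈ 1/√(35 × 0.1 × 0.9) = 0.56, and exp(1.96 × 0.56) ≈ 3, so about 3-fold either way.

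**6. Several characteristics together, if that were done.** With 35 attenders, simulated separation or no events occurs in 43% of trials for two binary plus one continuous characteristic, and in 52% for three binary plus two continuous.

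**7. If attender dropout were 20% instead.** 35 × 0.20 = 7 events. The 18/17 case falls to 0.8^18 + 0.8^17 − 0.8^35 = 0.018 + 0.023 − 0.000 = 4%. A 4/3 split gives SE = √(1/4 + 1/14 + 1/3 + 1/14) = 0.85, still about 5-fold either side.

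**8. The dropout proportion.** Four dropouts in 35 is 11.4%, exact 95% CI 3.2% to 26.7%. This is wide, but estimable and interpretable.

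**The case against.** The best defence is that the sentence is brief and flexible. It covers feasibility and lifestyle outcomes together, gives dropouts only as an example, and does not specify the estimator. Firth and exact methods are themselves forms of logistic regression, and a journal protocol often leaves such details to an analysis plan. This defence limits the point but does not remove it. The article names the outcome and the model class, and its own numbers show that the standard form of that model does not suit that outcome.

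Other parts of the defence stand:
- The 10% is stated for baseline to follow-up, with no arm given, so applying it to attenders is an inference. Losses before the first session do not count as dropout under the definition, so at that rate 3.5 is if anything high. On the other hand, 70 is a minimum, and the Contingency plan allows a larger sample.
- Reasons for dropout are already to be recorded (Intervention section), so the regression is not the only source of information about leavers.
- The Study design section says the pilot will supply attrition rates and help optimise the design. It ties no decision to predictors of dropout.

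Three stronger readings are tempting but not supported:
- **That a primary outcome cannot be estimated.** The primary outcome is the proportion, which can be; only its regression on characteristics is affected.
- **That the plan commits to multivariable models of dropout.** The article mentions univariate and multivariate models only for the Cox analysis of recovery time.
- **That the analysis would produce spurious significant predictors.** With 35 attenders and no association, the simulated Wald test rejected in only about 0.1% to 1.1% of trials. The risk lies in extreme point estimates and uninformative intervals.

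**Conclusion.** The point holds as a minor one. On the protocol's own sample size, and with its 10% loss rate carried over to session attenders, about 3 to 4 dropouts are expected. Standard logistic regression on a binary characteristic would then fail to give a finite odds ratio in roughly 30% to 50% of trials under no association, and would otherwise give intervals too wide to use. A single continuous characteristic usually gives a finite but imprecise estimate, so failure is common rather than certain.

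The result depends on the transferred 10% and on the assumed prevalences. Doubling the dropout rate, or counting all 70 participants, makes failure less frequent but leaves intervals of about 5-fold or more either side for a binary characteristic. The comparison of recovery time between arms is unaffected.

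**What to change.** In Data analysis and sample size, take dropout out of the general regression sentence and state three things:

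1. Dropout is reported as a proportion with an exact 95% confidence interval, and characteristics of dropouts and completers are tabulated with the recorded reasons.
2. If a model is kept for dropout, or for any other binary feasibility outcome with very few participants in the rarer category, it is Firth-penalised or exact logistic regression with one characteristic at a time, labelled exploratory and reported with intervals. Recruitment within 7 days may be such an outcome, because the eligibility criteria already require onset within the last 7 days.
3. Regression is kept for adherence measured per participant (sessions attended), where every attender contributes information.

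The cost is a few sentences, with no extra data. The loss is that no multivariable predictors of dropout would be reported, which the data could not support in any case.

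### The only between-arm contrast stated for a continuous secondary outcome is HADS change from baseline; regression on arm plus the baseline value would be more precise at negligible cost

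*Protocol article*

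**What the plan says.** The Protocol article's Introduction sets as secondary objectives "the effect of this intervention on cognitive function, adherence to the Mediterranean diet, physical function", followed by basic activities of daily living, anxiety and depression, quality of life, anthropometry and blood pressure. Under Secondary outcome measures, the Table 2 outcomes "will be also measured at baseline and follow-up at 3 months". Under Randomisation, "The participants will be randomly assigned (1:1) to the intervention or control group after the baseline assessment", so every baseline value precedes allocation.

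Data analysis and sample size names three sets of methods:

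- Linear or logistic regression, for "The associations between the social and clinical characteristics and feasibility" and lifestyle outcomes.
- Kaplan-Meier curves, the log-rank test and Cox regression, which compare the arms on recovery time only.
- A sample-size statement for HADS anxiety and depression, given as "mean differences of 5.5 and 6.0 in the changes observed" between arms, at 80% power and 5% significance with 35 per arm.

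Table 2 also describes the Senior Fitness Test results as a variation, which hints at change but names no model. Baseline adjustment is not mentioned for any secondary outcome.

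**The concern.** Two things do not meet. The secondary objectives ask what the intervention does, whereas the stated linear and logistic models ask which patients do well. A model with social and clinical characteristics as exposure does not estimate the randomised contrast.

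The one between-arm contrast given for a continuous secondary outcome is a difference in change. With one baseline and one follow-up value, a change score subtracts the whole baseline value, whatever its correlation with follow-up. That adds noise whenever the correlation is below 1. It also over-corrects for chance baseline differences between arms. With 35 per arm, such a difference has a standard error of √(2/35) = 0.24 SD even under perfect randomisation. In a pilot of 70, or about 63 after the expected 10% dropout, precision on the secondary objectives is scarce.

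**Working it through.** **Inputs.** From Data analysis and sample size: 35 per arm, 80% power, 5% significance, and detectable differences in change of 5.5 (HADS anxiety) and 6.0 (HADS depression). From Table 2: each subscale runs from 0 to 21. Assumed, because the article does not give them: a two-sided test, the baseline–follow-up correlation r, and equal SDs at both visits.

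**1. The plan's own figures.** The SD comes from a cited trial that is not shown, so 5.5 and 6.0 cannot be reproduced independently. Solving for the SD of change with the normal formula, SD = d / [(1.960 + 0.842) × √(2/35)] = d / 0.670:

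- anxiety: 5.5 / 0.670 = 8.21
- depression: 6.0 / 0.670 = 8.96

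Both differences equal a standardised effect of 0.67, so the pair is coherent.

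**2. Change score against baseline adjustment.** For visit SD s, the outcome variance per patient is:

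- change score: 2(1 − r)s²
- regression on arm and baseline (ANCOVA): (1 − r²)s²
- ratio: (1 − r²) / [2(1 − r)] = (1 + r)/2

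The detectable difference scales with the square root of this ratio. It does not depend on n, so it is the same with 63 patients as with 70.

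| Assumed r | Variance ratio | Detectable difference, anxiety / depression | Power at 5.5 / 6.0 |
|---|---|---|---|
| Change score, as stated | 1 | 5.5 / 6.0 | 80% |
| 0.3 | 0.65 | 4.43 / 4.84 | 93.5% |
| 0.5 | 0.75 | 4.76 / 5.20 | 89.9% |
| 0.7 | 0.85 | 5.07 / 5.53 | 86.0% |
| 0.9 | 0.95 | 5.36 / 5.85 | 82.0% |

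At r = 0.5, 70 patients analysed with baseline adjustment match 70 / 0.75 = 93 analysed on change.

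**3. Cost.** One degree of freedom moves the critical t from 1.9955 to 1.9960. Estimating the slope inflates the variance by about 1 + 1/(70 − 4) = 1.015. The gain is cancelled only when 1.015 × (1 + r)/2 = 1, that is at r of about 0.97.

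**4. Chance imbalance.** With equal SDs the within-arm slope on baseline is r. If one arm starts 1 point higher by chance, its expected follow-up excess is r points. The difference in change is then off by r − 1, which is −0.5 points at r = 0.5. Baseline adjustment removes this apart from error in the estimated slope.

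**5. A limit on r for HADS.** The implied visit SD is SD(change) / √[2(1 − r)]. On a 0–21 scale an SD cannot exceed 10.5. With change SDs of 8.21 and 8.96, that bound is passed once r exceeds about 0.69 (anxiety) or 0.64 (depression). So under equal SDs the last two table rows cannot hold together with the stated HADS figures: either r is lower or the borrowed SDs are too large. The article does not show which. The ratio (1 + r)/2 is unaffected.

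**The case against.** The strongest reply is that the article fixes no analysis here. The HADS sentence illustrates what the sample could detect, using another trial's results; it is not an analysis model. The regressions on patient characteristics suit a feasibility pilot and are not presented as estimates of the arm effect. Models for individual secondary outcomes are normally left to a fuller plan.

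Much of this stands. A reader might infer that all continuous secondary outcomes will be analysed as change scores. The text does not support that: change is stated for HADS and only hinted at for the Senior Fitness Test. A reader might also infer that the missing model for the other outcomes is an error. In a condensed article it is not.

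The change contrast is also valid: under randomisation the difference in change is unbiased, and regression to the mean affects both arms equally in expectation. The imbalance argument therefore concerns the particular allocation obtained, not long-run bias. The gain depends on an r that the document does not give, and it shrinks to 10% of variance at r = 0.8 and 5% at r = 0.9.

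What the reply does not remove is that the only contrast on the page is less efficient than one using the same data, and that none of the linear or logistic models described has arm as exposure.

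**Conclusion.** The point holds as a recommendation on efficiency and clarity, not as a correction of a wrong figure. For HADS, where the article does state a contrast, baseline adjustment would cut variance by 35%, 25%, 15% or 5% at assumed r of 0.3, 0.5, 0.7 or 0.9, given equal SDs at both visits. The detectable differences would be about 4.4/4.8, 4.8/5.2, 5.1/5.5 or 5.4/5.9 instead of 5.5/6.0. The same ratio would apply to any other continuous outcome if it were analysed as change.

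A reader might go further and expect ANCOVA to give the full trial better-estimated SDs. It does not. The relative error of an SD is roughly 1/√(2 × df), about 8.6% with either 68 or 67 degrees of freedom. ANCOVA yields a smaller residual SD, not a more precisely known one.

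**What to change.** In Data analysis and sample size, state that the arm effect on HADS anxiety and depression, and on the other continuous Table 2 outcomes, is estimated by linear regression of the 3-month value on randomised arm and the baseline value of the same outcome. Report it as an adjusted mean difference with a 95% confidence interval. If a fuller plan already names such a model, one sentence pointing to it is enough. Label the regressions on social and clinical characteristics exploratory.

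Report the residual SD and the baseline–follow-up correlation for each outcome, since the pilot is meant to inform the size of a full trial. State the SD behind the 5.5 and 6.0 so that it can be checked against the 0–21 range.

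This changes wording only. The baseline values are already collected before randomisation, and neither the sample size nor the visit schedule changes.
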